### Outcome measures

Patient outcomes will be collected at clinic visits at baseline (pre randomisation) and 6 months post randomisation unless otherwise stated.

#### Primary outcome

The primary outcome measure is the comparison between pain NRS at 6 months between the screening trial and implantation strategy and the implantation-only strategy [19].

#### Secondary outcomes

Secondary outcome measures include: the proportion of patients achieving at least 50% and 30% pain relief at 6 months as measured on the NRS [19], health-related quality of life (EQ-5D) [20], function (Oswestry Disability Index) [21], patient satisfaction (Patients’ Global Impression of Change) [22] and complication rates.

A qualitative study using semi-structured interviews will be carried out in parallel for a total of 30 of the patients recruited in each centre (10 at each centre) to explore their views of the screening trial, implantation and overall use of the SCS device.

Self-reported information on healthcare utilisation and non-NHS costs will be collected from participants using a standardised questionnaire to include management of adverse events (AEs), interventions, investigations, medication, inpatient hospitalisations, A&E, reprogramming visits and other healthcare-related visits, plus out-of-pocket costs and absences from work.

### Data collection and visits

Along with data collection at baseline, all of the outcomes will be sought through routine pain clinic attendances at 3 and 6 months. All unscheduled visits will be recorded in a log. The type of data collected during these visits is listed in Fig. 1 (SPIRIT diagram and Additional file 1).

#### Baseline visit

Patients who have been identified as potential participants will be sent a patient information sheet to read prior to the baseline visit. An MDT assessment will have been undertaken and the patient deemed suitable for SCS prior to the baseline visit. In the clinic, full written informed consent will be taken by the Principal Investigator or sub-investigator at the site or a suitable person as per the Delegation Log. Informed consent will be obtained during this visit.

#### Implant visit

Subjects who are randomised to the screening trial and implantation strategy will undergo two procedures as per usual clinical practice with a trial procedure and, if successful, a permanent implant in a second procedure. Details of the trial procedure will be as per usual clinical practice at the centre. Subjects who are randomised to the implantation-only strategy will undergo one procedure with the trial and permanent implant in one procedure. Wound care and management of the trial leads will be conducted as per the centre’s usual clinical practice regardless of trial randomisation.

#### One-month telephone interview following permanent implant (optional)

Subjects who have consented to undergo the qualitative interview and who have been randomised to do so will undergo a second interview.

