### Hypothesis and aims

We hypothesise that a no-SCS screening trial strategy will be superior to an SCS screening trial and more cost-effective. Specific aims of this study are to:compare the patient-related outcomes of an SCS screening trial strategy to a no-trial implantation-only strategy;determine the diagnostic performance (e.g. sensitivity and specificity) of an SCS screening trial;compare the cost-effectiveness of a screening trial strategy to a no-test implant-only strategy; andassess the expectations and experiences of patients for the use of an SCS screening trial.

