### Interventions

#### Screening trial and implantation strategy (usual care)

Patients randomised to this arm will receive a screening trial. A screening trial will consist of passage of either an external or internalised tunnelled SCS lead or leads attached to an external stimulator as per the centre’s routine practice. Those patients who have a successful screening trial will receive an implantable neurostimulation system while unsuccessful patients would not receive such an implant. Taking into consideration the RCTs included in the clinical evidence section of NICE TA159 [15], a successful screening trial will be defined as ≥ 50% pain relief and satisfactory on-table paraesthesia coverage (i.e. ≥ 80%) of the pain area, reduction in pain medications or improved quality of life and function, and successful location of leads at the anatomical target for paraesthesia-free therapies [10, 17]. Patients with an unsuccessful screening trial will not be implanted but all patients will continue follow-up to 6 months. Successful trial patients will go on to have the implantable pulse generator (IPG) implanted on a separate occasion.

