### Qualitative analysis

All subjects will be consented to take part in both the RCT and the optional qualitative study at the outset. A semi-structured telephone interview will be carried out with 30 patients recruited by purposive sampling (among those consenting) at three sites (at baseline and 1 month post implantation). Baseline interviews will explore the impact of pain on daily living, thoughts and understanding of the screening trial and implantation only and expectations of the spinal cord stimulator. One-month follow-up interviews will revisit thoughts and understanding of the spinal cord stimulators, expectations and explore their overall experience of the SCS device. Ten patients will be recruited from each centre, five from each treatment arm. Open-ended questions will be used to allow patients to express their own viewpoints. The interviews will be audio recorded and transcribed. Data will be analysed using thematic analysis [29, 30], facilitated by NVivo qualitative analysis software. The data will be interpreted as follows:themes emerging for the total patient group; andthemes emerging for the patients grouped by arm of the study (screening trial/implantation only).

In addition, participants will be asked to reflect and explore their experience of being in the study and evaluate things that went well, as well as to provide suggestions for changes and to complete a purpose-designed 5-point scale indicating their overall preference in relation to the two options (screening trial/implantation only).

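### The only post-procedure interview is timed from permanent implant, so patients who fail the screening trial have no scheduled interview about their experience of it

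*Protocol article*

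**What the plan says.** The fourth aim, in Hypothesis and aims, is to assess "the expectations and experiences of patients for the use of an SCS screening trial". It has two parts, expectations and experiences.

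Qualitative analysis plans telephone interviews with 30 patients "at baseline and 1 month post implantation". The visit schedule gives the second interview the same anchor in its heading, "One-month telephone interview following permanent implant (optional".

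The two interviews differ in content:
- Baseline: "Baseline interviews will explore the impact of pain on daily living, thoughts and understanding of the screening trial and implantation only", together with expectations of the stimulator.
- Follow-up: "One-month follow-up interviews will revisit thoughts and understanding of the spinal cord stimulators, expectations and explore their overall experience of the SCS device".

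On the sample, "Ten patients will be recruited from each centre, five from each treatment arm". Themes are then to be interpreted for the whole group and by arm.

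On what happens after a failed screening trial, the Interventions section says: "Patients with an unsuccessful screening trial will not be implanted but all patients will continue follow-up to 6 months".

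On how interviewees are chosen, the visit schedule says that consenting subjects "who have been randomised to do so will undergo a second interview", whereas Qualitative analysis specifies purposive sampling.

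**The concern.** An interview dated from implantation has no date for a patient who is never implanted. In the screening arm, those patients are exactly the ones whose screening trial failed. The baseline interview cannot stand in for the missing one, because baseline precedes randomisation and so precedes any experience of the procedure.

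Followed literally, the schedule selects the screening-arm accounts of experience on the result of the procedure that the fourth aim is meant to examine. Patients who went through a lead insertion and a test period without gaining an implant may see the screening trial quite differently from those who passed. When themes are compared by arm after the procedure, the screening arm is represented by its successes. The implantation-only arm is represented by everyone who met the on-table criteria.

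The article criticises earlier studies for lacking outcome data on patients who failed screening (Evidence for SCS screening trials as a predictor of long-term success). Its own qualitative component risks a similar gap.

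**Working it through.** **1. The plan's own count.** Three centres × 10 interviewees = 30, which reproduces the stated total. Three centres × 5 per arm = 15 interviewees in the screening arm.

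**2. Who has a date for each interview, reading the sections together.**

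| Interviewee | Baseline interview | Second interview |
|---|---|---|
| Screening arm, passed | yes | 1 month after implant |
| Screening arm, failed | yes | no date given |
| Implantation-only, implanted | yes | 1 month after implant |
| Implantation-only, not implanted (on-table criteria not met) | yes | no date given |

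The expectations part of the fourth aim therefore draws on all 30. The experience part, within the screening arm, draws on the first row only.

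**3. Illustrative size.** The article gives no expected failure rate for this trial. It does cite screening results from other studies, used here as an assumed range. With failure rate f among 15 interviewees:
- expected number without a second interview = 15 × f
- chance that at least one is affected = 1 − (1 − f)^15

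| Source cited in the article | f | 15 × f | Chance of at least one |
|---|---|---|---|
| Trial against conventional medical management, 95% success | 5% | 0.75 | 1 − 0.95^15 = 54% |
| High-frequency arm, 90/97 eligible | 7/97 = 7.2% | 1.08 | 67% |
| Conventional arm of the same trial, 81/92 eligible | 11/92 = 12.0% | 1.79 | 85% |
| Trial against reoperation, 19/24 | 5/24 = 20.8% | 3.1 | 1 − (19/24)^15 = 97% |
| Study with 75% relief in the trial period | 25% | 3.75 | 99% |
| Prospective cohort, 34/55 | 21/55 = 38.2% | 5.7 | 1 − (34/55)^15 = over 99% |

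On this range, between about 14 (15 − 0.75) and 9 (15 − 5.7) of the 15 would reach the second interview, and every patient missing for this reason would be a screening failure.

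**4. Topics.** The listed follow-up topics concern the stimulator, expectations and experience of the device. Experience of the screening trial is not among them. A new date alone would not fill the gap, because the topics also presuppose an implanted patient.

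**5. Selection of interviewees.** Being randomised to the interview and being purposively sampled are different procedures, and the two sections cannot both be right. This conflict is separate from the timing problem and adds nothing to its size.

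**The case against.** The strongest reply is that exclusion is inferred and not stated. The three-month and six-month visits also carry a heading that refers to permanent implant, yet the text beneath says that all patients attend. The Interventions section likewise keeps failures in follow-up to six months. So the phrase may be used loosely, and the text under the interview heading does not restrict the interview to implanted patients. The secondary outcomes section also says the interviews cover views of the screening trial. Finally, this is a condensed article, and Fig. 1 and Additional file 1, which list visit content, are not shown.

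Part of this stands: the documents leave a gap and do not state an exclusion. It does not dispose of the point. The later visits have a sentence that brings in everyone, and the interview has none. Qualitative analysis puts the implant timing in its running text, not only in a heading, and lists topics centred on the device. The problem is a timing rule that the article states twice, which is more than omitted operational detail.

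A reader might go further and infer that patients who fail are never interviewed about the screening trial, or that the whole fourth aim rests on those who passed. The documents do not support that. Future failures are interviewed at baseline on their understanding and expectations, and implantation-only patients contribute too. A reader might also infer that the five-point preference scale and the reflection on being in the study are lost for failures. Neither item has a stated time point, so that loss is possible but not shown.

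The objection to the arithmetic is also fair. The rates come from other populations and other trial methods, success here is a composite definition, and a purposive sample is not a random draw.

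**Conclusion.** The point holds for the experience part of the fourth aim, within the screening arm. As written, the only post-procedure interview has no date for patients who fail the screening trial, so accounts of having gone through it would come only from those who passed. The post-procedure comparison of themes by arm inherits that selection. Expectations are not affected.

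The illustrative size is about 0.8 to 5.7 of 15 screening-arm interviewees without a second interview. This assumes that interviewees fail independently and at rates borrowed from other studies. It also assumes that the timing is applied literally. The conclusion does not depend on the exact number, since every patient lost through the rule is of one kind.

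The point concerns a nested, optional component. It does not touch the primary outcome, the diagnostic performance analysis or the economic evaluation. It is still worth correcting, because a named aim is affected and the change is small.

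**What to change.** In both the one-month interview section and Qualitative analysis, time the second interview at one month after the last study procedure. That is the permanent implant or, for patients not implanted in either arm, the end of the screening or on-table trial. State that non-implanted patients remain in the purposive sample and are offered the second interview. Add experience of the screening trial to the follow-up topics, with a version of the guide for patients who have no device.

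In the same revision, reconcile the randomised selection in the visit schedule with the purposive sampling in Qualitative analysis, so that one method of choosing interviewees is stated.

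The cost is a small topic-guide adaptation and a protocol amendment, which Trial Management Group says must go to the ethics committee. Recruitment began in June 2017, so the change may come too late for some early interviewees. No extra interviews are needed: two per patient for 30 patients are already planned.

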#### Three-month and 6-month (end of study) visit following permanent implant

All patients will attend the clinic for the 3-month and 6-month appointments. Following the 6-month visit the patient will exit the study and be passed back to usual care within the pain clinic for ongoing management for the spinal cord stimulator.

#### Data collection and follow-up for withdrawn subjects

If a patient withdraws from the trial treatment, then they will be followed up wherever possible and data collected as per protocol until the end of the trial. The only exception to this is where the patient also explicitly withdraws consent for follow-up. Subjects who withdraw from the study will be initially invited to attend a follow-up appointment by letter. In the case of no response, the subject will be contacted by telephone twice over a 2-week period.

### Statistical analysis

#### Diagnostic performance

Analyses will be conducted and reported in accord with STARD recommendations [24]. Cross-tabulation will be used to report the SCS test results (fail versus pass) versus SCS pain relief (≥ 50% versus < 50%) at 6-month follow-up. Sensitivity will be determined as the percentage of participants with ≥ 50% pain relief at 6 months who pass the test, and specificity as the percentage of participants with < 50% pain relief who fail the test. Positive and negative likelihood ratios will be also calculated and reported. All results will be reported with 95% CIs.

#### Comparison of effectiveness

Analyses will be conducted and reported in accord with CONSORT recommendations [25]. We will closely monitor the process of data collection during the trial and provide a flow diagram summarising, by group, the numbers approached, recruited, randomised, followed up/lost to follow-up and outcome completion (Fig. 2). Primary analyses will be conducted on an intention-to-treat basis (i.e. according to randomised group) and to compare primary and secondary outcomes at 6-month follow-up between randomised groups on those with complete datasets. Outcomes will be compared using linear regression methods adjusting for baseline outcome scores and stratification/minimisation variables. Additional secondary analyses will be performed. Primary and secondary outcomes will be compared at 3 months as already described. The influence of missing data will be investigated using sensitivity analyses that make different assumptions, such as “best” and “worst” case scenarios depending on outcome type, as well as using multiple imputation methods. Exploratory analyses using interaction terms will be used to assess the potential subgroup effects according to stratification and minimisation variables.

**Fig. 2 Fig2:**
[figure not shown]
Consolidated Standards Of Reporting Trials (CONSORT) flow diagram

No interim or subgroup analyses are planned. All analyses will be undertaken using STATA v.14. A detailed statistical analysis plan will be prepared before any data analysis is conducted and agreed with the Trial Steering Committee (TSC)/Trial Management Group (TMG).

The study team will have access to the final trial dataset.

### Economic evaluation

An economic evaluation will be carried out to estimate the cost-effectiveness of a screening trial and implantation strategy versus an implantation-only strategy. Healthcare resource utilisation (e.g. management of AEs, interventions, investigations, medication, inpatient hospitalisations, A&E and other healthcare-related visits, plus out-of-pocket costs and absences from work) will be collected for each patient during the study follow-up period using data collection methods which have been successfully adopted by the applicants in previous studies [10, 23]. Resources required for the specific screening trial and implantation interventions will be recorded within the trial.

Items of resource use will be costed using national averages obtained from national sources (such as the Personal Social Services Research Unit, the British National Formulary and NHS reference cost databases) [26–28]. Cost components will be combined to derive total patient-level costs for the NHS. In addition, non-NHS costs such as productivity loss due to absence from work or patient out-of-pocket expenses will also be quantified to provide a full picture of how the strategies being compared will affect the financial burden imposed by the condition on both the NHS and the patients. Generic health-related quality of life (HRQoL) data will be collected using the EQ-5D-5L instrument. Both resource utilisation (costs) and the EQ-5D-5L will be collected at each follow-up visit. A within-trial cost consequence analysis will be carried out to estimate mean resource utilisation, costs, EQ-5D scores and total quality-adjusted life-years (QALYs) in each group, together with relevant measures of sampling uncertainty. QALYs will be calculated using the area under the curve approach, with regression-based adjustment for baseline EQ-5D score. The economic evaluation will take the form of a cost–utility analysis, to calculate the cost per additional QALY gained. Base-case analyses will be conducted from the NHS perspective, with additional analyses from the societal perspective. Deterministic sensitivity analysis will be undertaken to explore the robustness of the results to plausible variations in key assumptions and variations in the analytical methods used. In order to account for uncertainty, probabilistic sensitivity analysis (PSA) will also be undertaken using bootstrapping and the bootstrapped cost–effect pairs will be graphically presented on a cost-effectiveness plane. Cost-effectiveness acceptability curves will be constructed to show the probability that the intervention is cost-effective for specific thresholds of cost per QALY gained.

A two-stage economic model will also be developed with a decision tree reflecting the outcomes of the first 6 months and reproducing the observed TRIAL-STIM Study outcomes. After this 6-month period, a Markov “state transition” model will then extrapolate the evolution of patient outcome and costs over a period of 15 years. The model will be populated with data from the trial itself and previously published research. Again, extensive deterministic and probabilistic sensitivity analysis will be undertaken.

### Qualitative analysis

All subjects will be consented to take part in both the RCT and the optional qualitative study at the outset. A semi-structured telephone interview will be carried out with 30 patients recruited by purposive sampling (among those consenting) at three sites (at baseline and 1 month post implantation). Baseline interviews will explore the impact of pain on daily living, thoughts and understanding of the screening trial and implantation only and expectations of the spinal cord stimulator. One-month follow-up interviews will revisit thoughts and understanding of the spinal cord stimulators, expectations and explore their overall experience of the SCS device. Ten patients will be recruited from each centre, five from each treatment arm. Open-ended questions will be used to allow patients to express their own viewpoints. The interviews will be audio recorded and transcribed. Data will be analysed using thematic analysis [29, 30], facilitated by NVivo qualitative analysis software. The data will be interpreted as follows:themes emerging for the total patient group; andthemes emerging for the patients grouped by arm of the study (screening trial/implantation only).

In addition, participants will be asked to reflect and explore their experience of being in the study and evaluate things that went well, as well as to provide suggestions for changes and to complete a purpose-designed 5-point scale indicating their overall preference in relation to the two options (screening trial/implantation only).

### Safety monitoring

An AE is defined as any untoward medical occurrence in a patient during or following administration of an investigational product/procedure and which does not necessarily have a causal relationship with treatment. An AE can therefore be any unfavourable and unintended sign (including an abnormal laboratory finding), symptom or disease temporarily associated with the use of the trial device, whether or not considered related to the trial device. PIs will assess all AEs regarding their relationship to SCS. The SCS-related AEs include but are not limited to: occurrence of redness, tenderness or other sign of infection over the SCS implant site; observation of collections or other abnormalities over implant sites; shifting of the site of paraesthesia from the site originally intended, causing reduction in pain relief with inability to shift paraesthesia to the original position using programming; lead migration, either vertical or mediolateral; pain reports over implant sites; and patient reports of cessation of paraesthesia not remedied by reprogramming of the device. All adverse events will be followed until they have abated, or until a stable situation has been reached. Depending on the event, follow-up may require additional tests or medical procedures as indicated, and/or referral to the general physician or a medical specialist.

All clearly related signs, symptoms and abnormal diagnostic procedures or results will be recorded in the source document and grouped under one diagnosis. All adverse events occurring during the study period will be recorded. The independent members of the Steering Committee will be presented with the safety data prior to the Steering Group Meetings.

The trial is subject to the audit arrangements of the National Institute of Health Research (NIHR).

